**Methods:**

This is an approved open-label, multicenter, randomized controlled trial to compare the effectiveness of intranasal versus intravenous dexamethasone administered in low doses to moderate and severe COVID-19 adult patients. The protocol is conducted in five health institutions in Mexico City. A total of 120 patients will be randomized into two groups (intravenous vs. intranasal) at a 1:1 ratio. Both groups will be treated with the corresponding dexamethasone scheme for 10 days. The primary outcome of the study will be clinical improvement, defined as a statistically significant reduction in the NEWS-2 score of patients with intranasal versus intravenous dexamethasone administration. The secondary outcome will be the reduction in mortality during hospitalization.

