#### Procedures

After randomization, a Case Report Format (CRF) (printed or electronic) for each patient will be filled daily by the medical staff and completed at the end of treatment or fatal outcome, whatever occurs first. Blood and saliva samples will be collected every third day during the whole treatment to perform ancillary tests such as SARS-CoV-2 viral load, functional immunological assessment (lymphocyte cytometry, cytokine/chemokine profile), and cortisol levels, among other analyses.

All biological samples will be each 48 h at every hospital center participant, transported by a specialized service and concentrated at Instituto de Investigaciones Biomédicas (UNAM) to be managed and stored at − 70 °C until use. As mentioned in the Informed Consent, all samples will be used for the next 3 years. Additional biological samples may be taken at each hospital center when necessary, according to the treating physicians and will not be part of this protocol.

All personal data and medical information of the patients will be treated in a strictly confidential way. Only the lead investigator and the hospital coordinator investigators will have access to this information.

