#### Outcomes

The expected primary outcome is clinical improvement, defined as a two-point improvement in the ordinal scale regarding the initial NEWS-2 score. This is an adapted score recommended by the World Health Organization (WHO) and the National Institute for Health and Care Excellence (NICE) to facilitate the early recognition and escalation of deteriorating patients [55, 56]. Although this score is commonly adopted for triage, it can also be used for continuous assessment, particularly in predicting intrahospital mortality. In this context and based on previous experimental data regarding the sustained effect of intranasal dexamethasone, we decided to evaluate the improvement in the initial NEWS-2 score as the first outcome.

The secondary expected outcome includes a reduction in mortality that will be examined during treatment (after randomization), a reduction of the time required for mechanical ventilation, the length of patient’s stay in the hospital, 30-day post-discharge mortality, and intrahospital complications. Viral load, the immune-inflammatory profile, and other physiological parameters will also be evaluated before and after treatment (see above).

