#### Data collection and management

After acceptance and signature of the informed consent letter, patients will be randomized, saliva and nasopharyngeal samples will be taken to measure the viral load, and treatment will begin as indicated in Fig. 2. The patient’s clinical history will be based on the initial results and physical inspection. Blood and saliva samples will be collected before the start of DXM treatment and at days 3, 6, and 10 within the treatment period. All statistical analyses will be performed by our team of specialists.

The samples will be sent for specialized analysis following standardized operating procedures (SOP’s). All patient data, including clinical history and laboratory data, will be collected daily and managed using REDCap (Research Electronic Data Capture System) tools hosted at Instituto de Investigaciones Biomédicas, UNAM [57, 58].

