#### Plans to promote participant retention and complete follow-up

All participants will receive specialized medical care, including clinical, neurological, and neuropsychological studies. These evaluations will be carried out 1, 3, 6, and 12 months after COVID-19 to monitor the evolution of the disease. The participants that present any functional post-COVID decline will receive medical treatment and neurorehabilitation.

Likewise, patients who present an adverse effect or health problem during their participation in this study or derivate to it upon hospitalization will receive all necessary treatment and care until their resolution in the “Hospital General Hospital de Mexico [name].” In addition, patients will be monitored every 3 months for 1 year after the study. During the study, other immunomodulatory drugs such as colchicine, GM-CSF inhibitors, IVIG, interferons, interleukins inhibitors, and kinase inhibitors can be used under the responsibility of the physician.

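### The mortality outcome has inconsistent windows and omits in-hospital deaths after day 10; the duration outcomes do not allow for death, and the form's end is not reconciled with later events

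*Protocol article*

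**What the plan says.** The protocol article describes mortality in two places. The abstract's Methods paragraph says: "The secondary outcome will be the reduction in mortality during hospitalization". The Outcomes section lists "a reduction in mortality that will be examined during treatment (after randomization), a reduction of the time required for mechanical ventilation", followed by length of hospital stay, "30-day post-discharge mortality" and in-hospital complications. The abstract also fixes the treatment period: "Both groups will be treated with the corresponding dexamethasone scheme for 10 days".

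Three sections bear on how these outcomes are recorded:

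- Procedures says the case report form is filled in daily and "completed at the end of treatment or fatal outcome, whatever occurs first".
- Data collection and management says: "All patient data, including clinical history and laboratory data, will be collected daily and managed using REDCap". It gives no end date.
- The section on retention and follow-up plans later assessments: "These evaluations will be carried out 1, 3, 6, and 12 months after COVID-19 to monitor the evolution of the disease". It adds three-monthly monitoring for a year after the study.

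The article states no rule for patients who die in the ventilation-time or length-of-stay outcomes. The last-observation rule in Statistical analysis concerns the NEWS-2 components only.

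**The concern.** Patients enter this trial already needing oxygen or ventilatory support, so deaths in hospital beyond day 10 are plausible. If the main mortality outcome changes with the section being read, and one version leaves those deaths out, the mortality comparison is neither fixed in advance nor complete.

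Two of the windows also depend on discharge, which happens after randomisation and, in an open-label trial, is decided by staff who know the treatment arm. Post-discharge mortality concerns only patients who leave alive, so it does not compare the randomised groups as a whole.

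The two duration outcomes raise a related difficulty. Death ends both ventilation and stay. Where shorter means better and nothing in the definition accounts for death, an arm can gain on these outcomes because more of its patients die early.

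**Working it through.** **Mortality windows.** The plan gives no figure to reproduce here, so the check sets the definitions side by side. Days are counted from the start of treatment, taken to be the day of randomisation.

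| Outcome | Starts | Ends | Fixed from randomisation? |
|---|---|---|---|
| During treatment (Outcomes) | randomisation | planned day 10 | yes, as planned |
| During hospitalization (abstract) | admission or randomisation | discharge or death | no |
| 30 days post-discharge (Outcomes) | live discharge | discharge day + 30 | no |

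Applied to example patients:

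- Death in hospital on day 8: counted under the abstract and under Outcomes (during treatment).
- Death in hospital on day 15: counted under the abstract. Under Outcomes it is after treatment and not after a discharge, so it is counted in neither mortality outcome.
- Discharge on day 5: post-discharge follow-up ends on day 5 + 30 = 35. Discharge on day 25: it ends on day 25 + 30 = 55. The period at risk therefore differs between patients by the length of their stay.

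**Duration outcomes.** The documents give no mortality, stay or ventilation figures, so every input here is an assumption. Let m be mortality, S the mean stay of survivors and d the mean day of death. Then

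mean stay = (1 − m) × S + m × d,

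and raising mortality from m1 to m2 shortens the mean by (m2 − m1) × (S − d). With S = 14, m1 = 0.10 and m2 = 0.30:

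| d | Mean at 10% | Mean at 30% | Shortening |
|---|---|---|---|
| 4 | 12.6 + 0.4 = 13.0 | 9.8 + 1.2 = 11.0 | 2.0 days |
| 7 | 12.6 + 0.7 = 13.3 | 9.8 + 2.1 = 11.9 | 1.4 days |
| 10 | 12.6 + 1.0 = 13.6 | 9.8 + 3.0 = 12.8 | 0.8 days |

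The sign is that of S − d. The effect vanishes when deaths come on average at the survivors' mean stay and reverses when they come later.

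Ventilation time behaves the same way. Two assumed cases, each comparing 30% with 20% mortality among ventilated patients:

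- Survivors ventilated 15 days, deaths after 5 days: 0.3 × 5 + 0.7 × 15 = 12.0 against 0.2 × 5 + 0.8 × 15 = 13.0. The arm with more deaths looks one day better.
- Survivors ventilated 10 days, deaths after 15 days: 0.3 × 15 + 0.7 × 10 = 11.5 against 0.2 × 15 + 0.8 × 10 = 11.0. The arm with more deaths looks half a day worse.

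Ventilator-free days to day 28, with death scored 0, put the arm with more deaths behind in both cases: 0.7 × (28 − 15) = 9.1 against 0.8 × 13 = 10.4, and 0.7 × (28 − 10) = 12.6 against 0.8 × 18 = 14.4.

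**Form end against outcomes.** Of the five clinical secondary outcomes, mortality during treatment lies wholly within the planned 10 days. Post-discharge mortality always ends after day 10, since its window alone is 30 days. Ventilation time, stay and complications pass day 10 only in patients still in hospital then. Procedures names no source for data after the form is completed.

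**One-month contact.** It is timed after COVID-19 with no stated anchor. Eligibility requires more than 5 days of illness. If the month is 30 days from symptom onset, the contact falls earlier than day 30 − 5 = 25 after randomisation, so it does not by itself establish vital status at day 30.

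**The case against.** The article condenses a fuller protocol, and the analysis plan is not shown. A one-line listing of ventilation time and stay does not exclude a competing-risk or composite analysis, and mortality is reported beside them, so an excess of deaths would be visible. This part stands: a reader might infer that the secondary outcomes, as they will be analysed, reward early death, but the article does not specify that analysis, and the direction depends on when deaths occur. What remains is that the listed definitions can be shortened by death.

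A reader might also infer that the form closes before most of these outcomes occur, so that they cannot be measured. The documents do not support that. They give no figure for how much ventilation, stay or mortality falls after day 10, and they describe daily electronic capture without an end date and follow-up to 12 months. The form's closing point is unreconciled with later outcomes, which is a weaker statement.

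Nor are all the mortality windows outcome-dependent. Mortality during treatment starts at randomisation and has a planned length of 10 days. That criticism applies only to in-hospital and post-discharge mortality.

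Finally, in-hospital and post-discharge deaths can be seen as complementary components rather than rival versions. That would serve if Outcomes listed in-hospital mortality, but it lists mortality during treatment, and the gap between day 10 and discharge remains.

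**Conclusion.** The point holds for the mortality outcome on the article's own text. The abstract and Outcomes give different windows, and under Outcomes an in-hospital death after day 10 is in neither mortality outcome. Neither in-hospital nor post-discharge mortality has a fixed window from randomisation. How many deaths this affects cannot be derived from the documents.

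For ventilation time and stay the point holds conditionally: more deaths shorten both when deaths come earlier than survivors' extubation or discharge. The size, 0.8 to 2.0 days of mean stay for a 20-point rise in mortality, rests wholly on the assumed 14-day survivor stay and deaths at mean day 4 to 10.

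For data capture, the conclusion is limited to an unreconciled closing point and an unnamed source for later outcome data. These are secondary outcomes; the matter should be corrected, but it does not touch the primary comparison.

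**What to change.** 1. Define one mortality outcome: all-cause death within a fixed window from randomisation, for example 30 days, in all randomised patients. Use it in both the abstract and Outcomes, and report in-hospital and post-discharge deaths descriptively.
2. Define the duration outcomes so that death is the worst result or a competing event: ventilator-free days to day 28 with death scored 0, and time to discharge alive with death as a competing event.
3. Amend Procedures so that the form stays open to discharge and to day-30 vital status, and anchor the one-month contact to randomisation.

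The cost is revised outcome wording, a longer form page and a vital-status check timed from randomisation. The existing one-month contact can serve only once its timing is tied to randomisation.

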#### Data collection and management

After acceptance and signature of the informed consent letter, patients will be randomized, saliva and nasopharyngeal samples will be taken to measure the viral load, and treatment will begin as indicated in Fig. 2. The patient’s clinical history will be based on the initial results and physical inspection. Blood and saliva samples will be collected before the start of DXM treatment and at days 3, 6, and 10 within the treatment period. All statistical analyses will be performed by our team of specialists.

The samples will be sent for specialized analysis following standardized operating procedures (SOP’s). All patient data, including clinical history and laboratory data, will be collected daily and managed using REDCap (Research Electronic Data Capture System) tools hosted at Instituto de Investigaciones Biomédicas, UNAM [57, 58].

#### Plans to promote participant retention and complete follow-up

All participants will receive specialized medical care, including clinical, neurological, and neuropsychological studies. These evaluations will be carried out 1, 3, 6, and 12 months after COVID-19 to monitor the evolution of the disease. The participants that present any functional post-COVID decline will receive medical treatment and neurorehabilitation.

Likewise, patients who present an adverse effect or health problem during their participation in this study or derivate to it upon hospitalization will receive all necessary treatment and care until their resolution in the “Hospital General Hospital de Mexico [name].” In addition, patients will be monitored every 3 months for 1 year after the study. During the study, other immunomodulatory drugs such as colchicine, GM-CSF inhibitors, IVIG, interferons, interleukins inhibitors, and kinase inhibitors can be used under the responsibility of the physician.

#### Data monitoring committee

A multidisciplinary group of independent experts will be on charge to assess the progress, safety data, and if needed, critical efficacy endpoints of this study.

#### Data management

The information collected during the procedure will be documented physically and digitally in an exact and precise manner. Researchers will use complete patient reports along with the molecular and immunological tests to analyze the outcomes. The information collected will be treated as confidential, and only the global results will be published without showing the patients’ names. In case data are required, the information can be requested from the researchers with valid reasons.

#### Statistical analysis

Descriptive statistics using mean (standard deviation) or frequency (percentage) will be used following the dimension scale of the variable. An initial comparison between the hospital will define relevant differences among them. Since healthcare conditions are variable in each hospital included in this study, we will analyze the results with a multilevel mixed longitudinal model. The outcome analysis for NEWS-2 components (i.e., respiration rate, oxygen saturation, systolic blood pressure, pulse rate) will be done using the last observation carried forward (LOCF) in those subjects with at least two observations, this analysis will avoid over-optimistic estimates of efficacy. Other efficacy variables like biochemistry or cell counts will be analyzed without ITT due to the susceptibility to type II error.

Biochemical variables and cell counts will be aggregated using principal component analysis and use the scores if the Kaiser-Meyer-Olkin (KMO) is greater than 0.6 and sphericity *p* < 0.0001. The scores using varimax rotation will be used as dependent variables if the method is suitable for our data. The longitudinal mixed model can be described as:
$$ {y}_{ij}={X}_{ij}\beta +{u}_i+{v}_{j(i)}+{\epsilon}_{ij} $$

where *j* = 1,..,Ti are nested in 10 time points, within *i* = 1,..,5 hospitals. The Xs correspond to fixed variables like the treatments, age, sex, and weight, among other confounders.

A database in vertical format was reshaped to nest the biochemical, inflammatory markers, cell count adjusted by sex, age, and BMI. We will perform restricted maximum likelihood (REML) estimation in case we obtain balanced samples. However, if we obtain an unbalanced sample, we will use maximum likelihood instead [59]. Because we expect a small sample size from some hospitals, we will make inferences using the Kendward-Roger degrees of freedom method. We will make simultaneous inferences about l linear combinations of fixed factors. Despite the complicated situation where *l* > 1 we will consider:
$$ F=\frac{1}{l}{\left(\hat{\beta}-\beta \right)}^T\ L{\left({L}^T\ {\hat{\varphi}}_AL\right)}^{-1}\ {L}^T\ \left(\hat{\beta}-\beta \right) $$

The internal random structure [$$ {L}^T\ {\hat{\varphi}}_AL $$] can change in different settings, but still will be a good approximation. Simulations studies showed adequate performance of modifications with different REML [60]. Finally, the structure of residual error will be analyzed within the lowest-level group. Once recognized, the covariance structure we will use unstructured, Toeplitz, or exponential corrections. This approach will give unbiased approximation even in presence of unbalanced samples.

The residuals for our mixed models will be considered by the source of present variability: The marginal residuals will predict the marginal errors, the conditional residuals, and the best linear unbiased predictor (BLUP) residuals. The conditional residuals will be standardized with:

$$ {\hat{\varepsilon}}_k^{\ast }=\frac{{\hat{\varepsilon}}_k}{\sigma\ \sqrt{p_{kk}}} $$ , where *p*_*kk*_ represents the *k*th element of the covariance structure. These residuals are functions of the joint leverage of fixed and random effects.

Subgroup analysis will be based on interaction as secondary analysis. This information will help to identify multiplicative effects from basal conditions like the presence of type 2 diabetes, obesity, hypertension, clinical history IECA medication, or other conditions.

All analysis will describe the number of patients with the outcome of interests, the treatment effect (mainly using eta squared), additive and multiplicative interactions with 95% confidence intervals, and the direction of the interaction (positive or negative) by specific subgroups. The analysis will be performed with Stata version 17.0 [StataCorp LLC College Station TX]. A statistical difference with *P* < 0.05 will be considered significant.

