### Eligibility criteria

Inclusion criteria comprise patients of both sexes (non-pregnant female), aged from 18 to 90 years old, with presumptive SARS-CoV-2 infection and more than 5 days of clinical evolution, with moderate to severe symptoms requiring oxygen support or high flux mechanical ventilation (NEWS-2 ≥ 5), and abnormal CT-chest scan CO-RADS > 3. Patients should be diagnosed with atypical pneumonia, confirmed by chest images and oxygen saturation (SpO_2_) lower than 93% in ambient air or a ratio of the partial pressure of oxygen and the fraction of inspired oxygen (PaO_2_: FiO_2_) equal to or lower than 300 mmHg, and a positive RT- PCR SARS-CoV-2 test. These patients will be allocated into the experimental group or the control group in a 1:1 ratio (two arms) (Fig. 2) according to the randomization.

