**Fig. 2 Fig2:**
[figure not shown]
Outline of the REVIVAL trial clinical protocol. Initially, patients will be informed about the clinical trial; if they accept and sign the consent, they will be randomized using the Sealed envelope® software. Group A will receive intranasal DXM; Group B will receive intravenous DXM. Both groups will be sampled on days 0, 3, 6, and 10 post-treatment to collect sera and nasopharyngeal swabs. Patients will be monitored throughout the study. The results will be tested for statistical differences between groups

Exclusion criteria include patients with an RT-PCR SARS-CoV-2 negative test; previously receiving GCs at high doses by oral or intravenous administration; severely immunosuppressed as in AIDS, pregnancy, and autoimmune diseases; those who have received outpatient treatment with steroids for more than 72 h before hospital admission; those older than 90 years; with DXM allergy; risk for glaucoma; or recurrent respiratory diseases. Patients receiving other monoclonal antibody-based treatments such as tocilizumab are also excluded. No other concomitant treatments are prohibited for patient eligibility.

Elimination criteria include voluntary withdrawing, lack of informed consent letter, or imminent risk of death within 48 h.

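### LOCF on the NEWS-2 components, limited to patients with at least two observations, does not secure the promised protection against over-optimistic efficacy estimates

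*Protocol article*

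**What the plan says.** In the protocol article, Outcomes defines the primary outcome as clinical improvement, "defined as a two-point improvement in the ordinal scale regarding the initial NEWS-2 score". Statistical analysis says of the study results that "we will analyze the results with a multilevel mixed longitudinal model", with 10 time points. For the NEWS-2 components it then specifies an analysis "using the last observation carried forward (LOCF) in those subjects with at least two observations, this analysis will avoid over-optimistic estimates of efficacy". This is the only missing-data rule given for NEWS-2. The next sentence takes biochemistry and cell counts out of intention-to-treat, which implies that NEWS-2 is analysed by intention-to-treat. Further on, the same section says that the mixed-model approach stays unbiased when the samples are unbalanced.

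Under Procedures, the case report form "will be filled daily by the medical staff and completed at the end of treatment or fatal outcome, whatever occurs first". Death appears under Outcomes only as a secondary outcome, and no section says how it enters the NEWS-2 analysis. The text after Fig. 2 adds: "Elimination criteria include voluntary withdrawing, lack of informed consent letter, or imminent risk of death within 48 h".

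**The concern.** LOCF is presented as a safeguard, but in this population a main reason for a NEWS-2 series to stop early is death. Carrying the last living value to the end of the series scores such a patient as stable, or as improved if that value was two points better than baseline. The two-observation condition selects patients on what happens after randomisation, and those it removes are the earliest deaths and withdrawals. That conflicts with the implied intention-to-treat status of NEWS-2. The trial is open-label, so withdrawal may also differ by arm.

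If carried values enter the mixed model, they are treated as real measurements. Runs of identical values distort the within-patient correlation that the plan intends to model, and the model does not need them, because the plan itself says it copes with unbalanced data.

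At stake is the primary comparison in a 120-patient trial. A difference pulled toward zero could also matter at the interim analysis, where the study may be ended if no trend is seen.

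**Working it through.** The plan states no figure to reproduce here: it gives no death rate, NEWS-2 response rate or amount of missing data. Every input below is therefore an assumption.

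- m: proportion of an arm that dies; 10-30%
- r: response among survivors; 60% in both arms
- q: share of carried pre-death values that count as a two-point improvement; 10-50%
- e: share of deaths that occur before a second observation; 0-50%

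Reference, with all randomised patients analysed and death counted as not improved: (1 - m)r.

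LOCF with the two-observation condition: f(m) = [(1 - m)r + m(1 - e)q] / (1 - me). The denominator shrinks because the earliest deaths leave the analysis.

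**One arm.** With m = 20%, q = 30%, e = 25%, the reference is 0.80 × 0.60 = 48.0%. LOCF gives (0.48 + 0.20 × 0.75 × 0.30) / (1 - 0.05) = 0.525 / 0.95 = 55.3%. Over the whole grid the excess runs from 1 point (m = 10%, q = 10%, e = 0: 55.0% against 54.0%) to 16 points (m = 30%, q = 50%, e = 50%: 0.495 / 0.85 = 58.2% against 42.0%).

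**Between arms.** Take deaths of 20% intranasal and 10% intravenous. The reference is 48.0% against 54.0%, a difference of -6.0 points. Under the rule:

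| q | e | Intranasal | Intravenous | Difference (points) |
|---|---|---|---|---|
| 10% | 0% | 50.0% | 55.0% | -5.0 |
| 30% | 0% | 54.0% | 57.0% | -3.0 |
| 10% | 50% | 0.49 / 0.90 = 54.4% | 0.545 / 0.95 = 57.4% | -2.9 |
| 50% | 50% | 0.53 / 0.90 = 58.9% | 0.565 / 0.95 = 59.5% | -0.6 |

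With the death rates exchanged, the signs exchange: +6.0 becomes +5.0 to +0.6.

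**Direction.** Rearranging, r - f(m) = m(1 - e)(r - q) / (1 - me). With r, q and e common to both arms and q below r, this grows with m. The arm with more deaths keeps the lower response rate, so the difference shrinks but does not change sign. At the boundary q = 0 and e = 0, f(m) equals the reference and the rule does no damage.

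**The case against.** Five points can be made for the plan.

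1. A reader might infer that LOCF also favours ventilated patients, since eligibility includes those "requiring oxygen support or high flux mechanical ventilation". The documents do not support that. Recording is daily until the end of treatment or death, and nothing says it stops at ventilation, so these patients' values are observed and not carried. What vital signs mean under respiratory support is a separate measurement question.

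2. A reader might infer that the rule can create a false benefit. This is not shown. Under the assumptions above the difference only shrinks. If deaths are fewer on intranasal treatment, as the trial hopes, the estimate is indeed less optimistic. In that direction the plan's statement is right. It fails in the other direction, where excess deaths on the experimental arm are partly hidden.

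3. The article is a condensed text. A death rule may stand in a fuller document, and the article does not say outright that carried values enter the mixed model or the two-point responder outcome. This stands as a limit: the handling of death is inferred from the rule and the absence of an exception. But the article itself fixes the LOCF rule, its restriction and the unconditional promise.

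4. With daily recording, only losses at the very start have fewer than two observations, so that exclusion may be small. This stands; its size cannot be computed. The elimination criteria may remove some of the same patients separately.

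5. Counting ventilation as failure might seem a natural companion remedy. It would redefine the primary outcome and is not proposed here.

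**Conclusion.** The point holds in this limited form: the stated rule does not guarantee protection against over-optimism, and it fails when deaths are more frequent on the experimental arm. As written, it carries living values past death and omits some randomised patients from an analysis implied to be intention-to-treat. It also adds nothing to a mixed model that the plan already regards as adequate for unbalanced data.

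Under the assumed inputs, a 6.0-point difference in either direction is reduced to between 5.0 and 0.6 points. These figures show direction and plausible scale; they are not estimates for this trial. They rest on equal r, q and e in the two arms, and on carried values reaching the responder outcome. Distortion of the within-patient correlation depends on carried values also being fed to the mixed model.

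**What to change.** In Statistical analysis, delete LOCF, the two-observation condition and the claim about over-optimism. In their place state that:

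- all randomised patients are analysed in the arm to which they were allocated;
- in the two-point NEWS-2 responder outcome, death by day 10 counts as not improved, and discharge alive before day 10 is scored by status at discharge;
- the longitudinal mixed model is fitted to observed values only;
- a worst-case sensitivity analysis, allowing for data not missing at random, covers withdrawals.

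The elimination criteria should be aligned with the first item, so that withdrawal after randomisation does not by itself remove a patient from the analysis. The responder comparison, not the mixed model, should carry the deaths: a model fitted to observed values treats measurements after death as merely missing.

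The cost is wording and slightly more analysis work. Deaths, hospital stay and daily clinical data are already collected, and neither sample size nor trial conduct changes.

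### The printed mixed model has indices for hospital and time but none for the patient, so as written repeated values from one patient are treated as independent

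*Protocol article*

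**What the plan says.** All places are in the Protocol article, under Methods.

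- **Type of model** (Statistical analysis). Because care differs between hospitals, "we will analyze the results with a multilevel mixed longitudinal model".
- **Equation and indices.** The model is y_ij = X_ij β + u_i + v_j(i) + ε_ij, where j runs from 1 to Ti over values that "are nested in 10 time points, within" hospitals, i = 1 to 5.
- **Fixed part.** "The Xs correspond to fixed variables like the treatments, age, sex, and weight, among other confounders".
- **Residuals.** "Finally, the structure of residual error will be analyzed within the lowest-level group", and for the covariance "we will use unstructured, Toeplitz, or exponential corrections".
- **Test level.** P < 0.05.
- **Data.** The abstract has 120 patients randomised 1:1. Under Data collection and management, patient data are recorded daily, while for the study samples "Blood and saliva samples will be collected before the start of DXM treatment and at days 3, 6, and 10 within the treatment period".

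**The concern.** Treatment is allocated to patients and does not change within a patient, so the information about a treatment main effect comes from 120 patients. A valid longitudinal model must recognise that values from the same patient on different days are correlated. The printed equation has nothing that does this. Two values from one patient on different days share only the hospital effect u_i, exactly as values from two different patients in that hospital do.

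If the model were fitted that way, up to 120 × 10 = 1,200 patient-days would stand in for 120 patients in the standard error of the treatment effect. The standard error would be too small, and a treatment with no effect could be declared effective well above the stated 5%.

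**Working it through.** **1. Reading the equation.** The plan gives no figure of its own on this point beyond the 5% level, so the first step is textual.

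- If j is the time point, as the definition suggests, there is no patient term. Treatment, age, sex and weight differ between patients within one hospital-day, yet X_ij has no index to carry that difference. Also, v_j(i) and ε_ij then have the same index and cannot be separated unless the residual gains a patient index.
- If j is the patient, v_j(i) is a patient effect. The equation then has no time index and conflicts with its own definition.
- The residual structure applies within the lowest-level group. In the printed equation that group is time within hospital. The structures listed would help only if the group were the patient, and the text does not say so.

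The paragraph needs correction on either reading.

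**2. Size, if fitted with hospital and time-within-hospital effects only.**

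Inputs from the protocol: 120 patients, 5 hospitals, m = 10 daily values or m = 4 samples, and a 5% test (taken as two-sided). Assumed, because the documents do not give it: within-patient correlation ρ = 0.3, 0.5 or 0.7.

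For a treatment effect averaged over time, the variance is understated by the factor D:

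- Exchangeable correlation: D = 1 + (m − 1)ρ.
- AR(1), with ρ between consecutive values: D = 1 + (2/m) Σ (m − k) ρ^k, for k = 1 to m − 1.

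Actual α = 2[1 − Φ(1.96/√D)].

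Example, m = 10, ρ = 0.5, exchangeable: D = 1 + 9 × 0.5 = 5.5, √D = 2.345, 1.96/2.345 = 0.836, α = 0.403.

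Example, m = 10, ρ = 0.5, AR(1): Σ = 8.002, D = 1 + 0.2 × 8.002 = 2.600, √D = 1.613, α = 0.224.

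| m | Structure | ρ | D | α, formula | α, simulated |
|---|---|---|---|---|---|
| 10 | exchangeable | 0.3 | 3.7 | 0.308 | 0.304 |
| 10 | exchangeable | 0.5 | 5.5 | 0.403 | 0.423 |
| 10 | exchangeable | 0.7 | 7.3 | 0.468 | 0.471 |
| 10 | AR(1) | 0.3 | 1.73 | 0.137 | 0.141 |
| 10 | AR(1) | 0.5 | 2.60 | 0.224 | 0.224 |
| 10 | AR(1) | 0.7 | 4.16 | 0.336 | 0.338 |
| 4 | exchangeable | 0.3 | 1.9 | 0.155 | 0.148 |
| 4 | exchangeable | 0.5 | 2.5 | 0.215 | 0.202 |
| 4 | exchangeable | 0.7 | 3.1 | 0.266 | 0.275 |
| 4 | AR(1) | 0.3 | 1.55 | 0.116 | 0.115 |
| 4 | AR(1) | 0.5 | 2.06 | 0.172 | 0.183 |
| 4 | AR(1) | 0.7 | 2.71 | 0.234 | 0.230 |

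The simulation used 3,000 null trials per row, with 5 hospitals × 2 arms × 12 patients. The four samples were treated as equally spaced. Testing the same data at patient level gave 0.042 to 0.060 in every setting simulated.

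**3. A different test.** With a treatment-by-time slope and no patient level, the simulated α for ρ from 0.3 to 0.9 was:

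- exchangeable correlation: 0.000 to 0.019 (conservative);
- AR(1), 10 times: 0.105 to 0.189 (liberal);
- AR(1), four times: 0.001 to 0.057.

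**The case against.** The best reply is that this is garbled notation and the analysts know that patients are the subjects. Toeplitz and exponential structures depend on lag in time, so they make sense only for repeated values of one subject. The word longitudinal and the long-format data set point the same way. This is a fair inference about intent, and one cannot conclude that the residual structure certainly fails to cover the patient. But the grouping unit is never stated, and the equation and index definition that are printed exclude it. This is something stated wrongly, so it is not detail that an article may leave to a fuller document. The Kenward-Roger adjustment does not help either, since it corrects inference for the covariance that is modelled and cannot supply a missing level.

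The reply also limits the size, and that part stands. A reader might infer that the false-positive rate is simply 30-47%. That is the upper part of the range and needs exchangeable correlation, 10 values per patient and a time-averaged main effect. The plan mentions linear combinations of fixed factors without fixing which contrast is tested. For a comparison on a single day each patient contributes one value, and D does not apply.

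Three further inferences are not supported:

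- **That day, treatment-by-day or baseline NEWS-2 are wrongly left out.** The list of fixed variables is explicitly open.
- **That ten time points contradict all laboratory data.** The four days apply to the study blood and saliva samples. The same section says laboratory data are collected daily.
- **That the NEWS-2 responder endpoint itself is tested with this equation.** The general sentence on the mixed model may reach NEWS-2, but the equation follows directly on the principal-component scores for biochemistry and cell counts.

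**Conclusion.** The point holds as a misspecified model on the page: hospital and time are indexed and the patient is not, and the residual paragraph does not clearly repair this. If the model is fitted as written and treatment is tested as a time-averaged fixed effect, the type I error at a nominal 5% is about 14-47% with 10 time points and about 12-28% with four. These ranges rest on an assumed ρ of 0.3 to 0.7 and cover both exchangeable and AR(1) correlation. With lower correlation the excess shrinks: at ρ = 0.1 with four samples, exchangeable, D = 1.3 and α = 0.086. The direction is not universal, because a treatment-by-time slope test could be conservative. If the analysts already intend a patient level, the error is confined to the text, but it still has to be corrected.

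**What to change.** Restate the model with three levels: time t within patient i within hospital h. Index y and the residual by h, i and t. Include either a patient random effect or a residual covariance (unstructured, Toeplitz or exponential) stated to be grouped by patient, and define every index in words.

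For the blood and saliva variables, use the four sampling times (days 0, 3, 6 and 10). The gaps are 3, 3 and 4 days, so choose a structure that allows unequal spacing: unstructured, or exponential in actual days. Toeplitz by visit order assumes equal gaps.

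The cost is a rewritten paragraph and one more level, or a named grouping variable, in the Stata command. No new data are needed. The downside is that P values for the treatment effect will be less favourable than under the model as printed.
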